## Abstract

**Background:**

Autism Spectrum Disorders (ASD) are a collection of neurodevelopmental diseases characterized by poor social interaction and communication, a limited range of interests, and stereotyped behavior. High-functioning autism (HFA) indicates a subgroup of individuals with autism who possess cognitive and/or language skills that are within the average to above-normal range for their age. Transcutaneous auricular vagus nerve stimulation (taVNS) holds promise in children with HFA. However, few studies have used randomized controlled trials to validate the effectiveness of taVNS. Therefore, in this study, we intend to provide a study protocol to examine the therapeutic effects of taVNS in individuals diagnosed with HFA and to investigate the process of brain network remodeling in individuals with ASD using functional imaging techniques to observe alterations in large-scale neural networks.

**Methods and design:**

We planned to employ a randomized, double-blind experimental design, including 40 children receiving sham stimulation and 40 children receiving real stimulation. We will assess clinical scales and perform functional imaging examinations before and after the stimulation. Additionally, we will include age- and gender-matched healthy children as controls and conduct functional imaging examinations. We plan first to observe the therapeutic effects of taVNS. Furthermore, we will observe the impact of taVNS stimulation on the brain network.

**Discussion:**

taVNS was a low-risk, easy-to-administer, low-cost, and portable option to modulate the vagus system. taVNS may improve the social performance of HFA. Changes in the network properties of the large-scale brain network may be related to the efficacy of taVNS.

**Clinical trial registration:**

http://www.chictr.org.cn, identifier ChiCTR2300074035.

## Introduction

Autism Spectrum Disorders (ASD) are a collection of neurodevelopmental diseases characterized by poor social interaction and communication, a limited range of interests, and stereotyped behavior. (American Psychiatric Association, 2013) (1). Its prevalence has been rising gradually. According to the most recent survey conducted by the Centers for Disease Control and Prevention (CDC) ‘s Autism and Developmental Disabilities Monitoring (ADDM) Network in 2020, it is estimated that approximately 1 in 36 children had been diagnosed with ASD. The disorder affects all races and countries and has drawn tremendous attention (2).

ASD is a heterogeneous disorder. Even among individuals who meet the core diagnostic criteria for ASD, there is significant variability in intelligence (3). Low intelligence is often concomitant with ASD, and these patients are considered as low functioning autism. On the other side, patients with average or even above-normal cognitive and/or language skills are classified as high-functioning autism (HFA) (4). Patients with HFA usually have an IQ of at least 70 and demonstrate near-normal levels of language development (4, 5). However, they still exhibit notable deficits in socio-emotional function, language comprehension, and expressive abilities (6, 7). These sustained deficiencies in social behavior have wide-ranging consequences on the general functioning of the patients and hinder participation in meaningful occupations and important roles in society (4, 8, 9). It is worth noting that only a small percentage, ranging from 5% to 15%, of adults with ASD can achieve a relatively normal social life and acceptable levels of academic or occupational functioning (10). Additionally, few individuals with ASD attain enough independence to pursue marriage or homeownership (4).

Currently, there are no approved medications able to address the core symptoms of ASD, which include social communication difficulties as well as limited restricted and repetitive behaviors and interests (11). Available pharmacological treatments aim only to alleviate concomitant symptoms, including inattention, compulsions, hyperactivity, anxiousness, sleep disruption, and irritation (12). Applied Behavior Analysis (ABA), an evidence-based approach, is shown to be potentially beneficial in enhancing certain outcomes for individuals with ASD. However, it can be administered only by professional agencies, making it time-consuming, costly, and difficultly available (13, 14). Therefore, exploring innovative, effective, and applicable treatments for children with ASD is of great importance.

Neuromodulation has been applied successfully in treating many psychiatric diseases because of its unique advantage (15). Vagus nerve stimulation (VNS) is an effective neuromodulation therapy that received initial approval from the US Food and Drug Administration (FDA) for drug-resistant epilepsy in 1997 (16). After the discovery of the mood-altering effects of VNS, its use expanded to treat treatment-resistant depression and was approved by the FDA in 2005 (17, 18). In patients with intractable epilepsy and ASD, VNS not only provides seizure control but also alleviates symptoms of ASD, which implies a potential therapeutic effect of VNS for ASD (19).

However, the invasive nature of VNS has limited its usage in certain diseases. Transcutaneous auricular vagus nerve stimulation (taVNS) stimulates the ear directly with a non-invasive method (15, 20, 21), and it had a higher potential application value in ASD because of an omission of surgical intervention procedures. Studies have shown that taVNS can yield a comparative effect to traditional VNS, and the effect is primarily based on the anatomical fact that the ear is the sole site on the human body where the afferent vagus nerve distributes (22).

Social dysfunction is a prominent characteristic of ASD, encompassing impairments in emotion recognition, interception accuracy, and emotional memory (23). Prior studies have demonstrated that taVNS can enhance various aspects of social cognition, including social attention (24), social-emotional understanding and regulation (25), interception accuracy (26), and social cognitive flexibility (27). Therefore, taVNS may be a promising alternative treatment for individuals with ASD, offering potential improvements in social cognition. Notably, in an open-label trial of 12 individuals with ASD treated with taVNS, average scores for anxiety and sleepiness were improved (28). Inspired by the results of this preliminary trial, a more rigorous study is warranted to provide further validation of the therapeutic efficacy of taVNS in individuals with HFA.

ASD is widely acknowledged as a neurodevelopmental disorder affecting brain networks (29, 30). Previous neuroimaging studies have indicated that individuals with ASD exhibit atypical brain structure and connectivity, particularly in regions associated with social cognition, emotional processing, and language abilities (30, 31). Similar results have been found in patients with HFA (32, 33). Previous studies have demonstrated that taVNS exerts modulatory effect on cortical and subcortical areas of the brain in healthy adults (34) and aiding in the regulation of socio-emotional functions impaired in depression (35). Furthermore, the neuroplasticity of children’s brains is significant (36), and taVNS has the potential to enhance it further by modulating brain networks. However, there is currently a lack of studies investigating the impact of taVNS on brain network modification in children with HFA.

Based on the aforementioned evidence, we designed our protocol with two primary objectives: First, it aims to examine the therapeutic effects of taVNS in individuals diagnosed with HFA; Second, it intends to investigate the process of brain network remodeling after taVNS using functional imaging techniques. We will use graph-theoretic analysis to compare the brain network characteristics of individuals with HFA before and after receiving taVNS. Additionally, we will examine the differences in these characteristics between patients with HFA and healthy controls, considering both structural and functional connectivity perspectives. Our hypothesis posits that taVNS has the potential to enhance the efficiency and flexibility of brain networks in HFA patients, leading to an improvement in their social cognitive abilities.

## Methods/design

### Study design

The study will be a randomized, double-blind, sham-controlled clinical trial, which will include patients assigned to active taVNS and sham taVNS groups and healthy subjects assigned to a healthy control group (HC). The study timeline of events is listed in **Figure 1**. For included patients, this study consisted of three basic phases: (a) a one-week baseline; (b) a consecutive 12-week treatment period without weekend interruption (Week 1 - Week 12, W1-W12); and (c) a follow-up period of 12 weeks (Week 13 – Week 24, W13 - W24). After enrollment, an interview will be used to acquire general patient information, including age, gender, duration of HFA, family history, and results of the clinical assessment tools during the baseline. Following the baseline period, patients will be assigned to one of the two treatment groups randomly to receive active taVNS or sham taVNS treatment using a random number table, which will be generated by SPSS 25.0 before enrollment of the first patient. During the follow-up period, patients will be evaluated with clinical assessment tools as well as structural and functional imaging scans.

**Figure 1 f1:**
[figure not shown]
A schematic representation of the study timeline of events.

The treatment condition assignment will remain undisclosed to patients and independent observers who perform clinical assessments and MRI scan technicians until the last interview. Only the technicians performing the taVNS procedure and the physician assigning the randomization without patient contact will be aware of the group information. No communication will be allowed between patients during any phase of the study to maintain blindness.

Patients will be evaluated using the clinical assessment tools at five time points (baseline; W4, the first month of treatment; W12, right after treatment; W16, short-term follow-up; W24, long-term follow-up) (**Table 1**). MRI scan will be acquired at three time points (baseline, W12, and W24). More details regarding the clinical procedures can be found in **Figure 2**; **Table 1**. Healthy subjects in the HC group will be evaluated with the same clinical tools and undergo an MRI scan only once. The clinical endpoints are assessed by blinded observers who are not involved. Furthermore, all dropouts will be documented and reported, specifying the reasons for their withdrawal.

**Table 1 T1:** Measurements at each time point.

Measurements/time point	Recruitment	Baseline	4 weeks	12 weeks	16 weeks	24 weeks
Inclusion/exclusion criteria	√	N/A	N/A	N/A	N/A	N/A
Behavioral Checklist for Children with High-Functioning Autism/Asperger’s Disorder	N/A	√	√	√	√	√
ABC	N/A	√	√	√	√	√
CABS	N/A	√	√	√	√	√
SRS	N/A	√	√	√	√	√
WISC	N/A	√	√	√	√	√
MRI scanning	N/A	√	N/A	√	√	√

√, need to be finished; ABC, Autism Behavior Checklist; CABS, Clancy Autism Behavioral Scale; SRS, Social Responsiveness Scale; WISC, Wechsler Intelligence Scale. N/A, Not applicable.

**Figure 2 f2:**
[figure not shown]
Proposed study procedures and participant flow. HFA, high−functioning autism spectrum disorder; ABC, Autism Behavior Scale; CABS, Clancy Autism Behavioral Scale; SRS, Social Responsiveness Scale; HC, healthy controls; fMRI 、DTI.

This study is authorized by the ethical committee of Beijing Children’s Hospital and will be conducted in compliance with the Declaration of Helsinki. Informed written consent will be acquired from the children and/or their legal guardians.

### Participants

#### Recruitment of participants

The Beijing Children’s Hospital Department of Psychiatry will recruit participants with HFA diagnoses from clinical practice, and a clinical multidisciplinary team involving two experienced psychiatrists will diagnose patients according to the DSM-5 diagnostic criteria. The inclusion criteria are as follows:

the age range is between 6-12 years old.Wechsler intelligence test IQ of at least 80 for Chinese children.ability and willingness to cooperate with relevant assessments and tests.right-handedness.

The exclusion criteria include:

seizure disorder or other neurological diseases (including brain tumors and craniocerebral trauma).concomitant with other mental disorders, except for attention deficit hyperactivity disorder (ADHD) and obsessive-compulsive disorder (OCD).claustrophobia.impulsivity or aggression.presence of metal products in the body.

Discontinuation and withdrawal criteria:

sudden acute illness who are unable to progress to the next phase in the study.poor adherence, and biased results will be regarded as withdrawing from the study.other uncontrollable factors or self-withdrawal from the study.

In this study, recruitment is set to occur over a period of one and a half years (from August 2023 to December 2024). Beijing primary schools will be recruited to provide healthy controls meeting the following inclusion criteria:

The age range is between 6-12 years old.IQ of at least 80.right-handedness.

Exclusion criteria include:

diagnosis of neurological or mental disorders.claustrophobia.presence of metal products in the body.

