### Statistical analysis

Basic analyses will be conducted using SPSS 25.0 software. At baseline, independent samples t-tests will be used to determine if there is no statistical difference between the two intervention groups; paired samples t-tests will then be used to examine the differences between mean scores before and after the taVNS intervention to determine the effectiveness of the treatment. Additionally, for the imaging study, we will use two-sample t-tests to compare brain network parameters between the HC and sham groups, as well as paired-sample t-tests to determine brain network parameters between the sham and active groups. Based on age and gender as covariates, a two-sample t-test will be used to compare the small-world properties and global parameters of the anatomical network between the HC group and the sham group. The level of significance for all statistical tests is set at p< 0.05. A Bonferroni correction will be performed on the t-tests utilized to examine group differences in behavioral and brain measurements, to account for multiple comparisons.

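### The planned HFA-versus-healthy network contrast mixes HFA with ADHD and OCD, which patients may have and controls may not; record status and add a restricted companion contrast

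*Protocol article*

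**What the plan says.** All references are to the protocol article.

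- **Patients (Recruitment of participants).** Children are excluded if they are "concomitant with other mental disorders, except for attention deficit hyperactivity disorder (ADHD) and obsessive-compulsive disorder (OCD"). ADHD and OCD are thus admitted, with no cap and no stratification. The same list excludes "impulsivity or aggression".
- **Controls (same section).** Any "diagnosis of neurological or mental disorders" is an exclusion.
- **Aim (end of the Introduction).** After the before-and-after comparison in patients, the text adds that "we will examine the differences in these characteristics between patients with HFA and healthy controls".
- **Matching (Abstract, Methods and design).** "we will include age- and gender-matched healthy children as controls".
- **Analysis (Statistical analysis).** "we will use two-sample t-tests to compare brain network parameters between the HC and sham groups"; no covariates are named for this comparison. For the anatomical network only: "Based on age and gender as covariates, a two-sample t-test will be used to compare the small-world properties and global parameters", again HC versus sham. Bonferroni correction is planned for the t-tests on group differences.
- **Not found in the article.** Table 1 has no ADHD or OCD measure. No adjustment, subgroup or sensitivity analysis for ADHD/OCD is described, and the Limitations section does not raise the matter.

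**The concern.** Diagnosed ADHD or OCD can occur in one group and is barred from the other by design. Age and gender matching does not balance it, and age and gender covariates do not remove it. Nor does a larger control group, which only estimates the same mixed quantity more precisely.

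At stake is the interpretation of one family of results. A network difference produced partly or wholly by ADHD or OCD could be reported as a characteristic of HFA. Medication for these conditions could contribute in the same way: the eligibility lists contain no medication criterion, and the article does not say how many children take any.

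**Working it through.** **1. The plan's own figure.** The article computes no figure for the control contrast. Its one calculation is the patient sample size on the CABS (mean paired difference 5, SD 8, alpha 0.05, power 0.9). With a two-sided normal approximation:

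- n = (8 × (1.960 + 1.282) / 5)² = 26.9, so 27
- 27 / (1 − 0.20) = 33.75, so 34
- 34 / (1 − 0.15) = 40

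This reproduces the stated 34 and 40 per patient group. It does not bear on the point, except that 40 is the size of the sham arm. No number of healthy controls is stated.

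**2. What the planned contrast estimates.** Let p be the share of HFA children with ADHD or OCD, d the effect of that comorbidity (or its treatment) on a network metric in SD units, and h the difference due to HFA alone. Diagnosed comorbidity is zero among controls, so

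expected difference = h + p × d.

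Age and gender adjustment leaves p × d in place.

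**3. Size, under assumed inputs.** The article gives neither p nor d. Assumptions: p from 0.30 to 0.70, d from 0.3 to 0.5 SD, 40 controls.

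- Low end: 0.30 × 0.3 = 0.09 SD
- High end: 0.70 × 0.5 = 0.35 SD

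For a two-sample t-test, the noncentrality is shift / √(1/n₁ + 1/n₂). With 40 versus 40 the root is 0.2236, giving 0.40 and 1.57. The chance of p<0.05 when h = 0 is:

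| Shift | 40 vs 40, unadjusted | 34 vs 34, unadjusted | 40 vs 40, at 0.05/7 |
|---|---|---|---|
| 0.09 SD | 6.8% | 6.5% | 1.2% |
| 0.35 SD | 34% | 30% | 12% |

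The 34 is 40 × (1 − 0.15), the article's invalid-MRI rate. The divisor 7 is an assumption: the article does not define the Bonferroni family, and seven is the count of small-world (five) plus global (two) metrics under Network analysis. The nominal rates are 5% unadjusted and 0.7% per metric at 0.05/7.

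For scale, 40 versus 40 detects 0.63 SD at 80% power, so the shift is 0.09/0.634 = 14% to 0.35/0.634 = 55% of the detectable difference.

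**4. Can the two be separated?** Yes, if status is recorded. Comorbidity varies among the patients, so a model with group and comorbidity terms is estimable, and a contrast restricted to HFA children without ADHD/OCD contains no p × d term. The price is precision. At p = 0.70, with 40 controls and 80% power at unadjusted p<0.05:

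- sham arm only: 40 × 0.30 = 12 versus 40, detectable difference about 0.94 SD
- both arms pooled at baseline: 80 × 0.30 = 24 versus 40, about 0.73 SD

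At p = 0.30 the sham-only contrast keeps 28 versus 40. Its standard error is √(1/28 + 1/40) / √(2/40) = 1.10 times that of the full sham contrast.

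**The case against.** The strongest reply is that nothing here is an error. Controls without mental disorders are what healthy controls means, and admitting ADHD and OCD is an open choice that helps generalisability. The Introduction promises differences between patients with HFA and healthy controls, not effects net of comorbidity. This stands as far as it goes: HFA as enrolled versus healthy is a legitimate contrast. The difficulty arises when its result is attributed to HFA itself, and the plan gives a reader no means of judging that.

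Four stronger readings are tempting, and the article does not support them.

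- *The HFA difference cannot be separated from ADHD/OCD.* True of the planned analysis, not of the design; restriction or a comorbidity term separates them.
- *ADHD/OCD status will not be collected.* The list of baseline interview items under Study design is introduced as inclusive, not exhaustive, and case-report fields are commonly left to the full protocol. The psychiatrists must in any case assess comorbid diagnoses to apply the exclusion.
- *The control difference is the yardstick for brain-network remodeling.* No section says so. The second objective concerns change after taVNS, and the control comparison is introduced as additional.
- *The trial's efficacy result is compromised.* Active versus sham is protected by randomisation in expectation, and within-patient change does not use controls.

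Excluding impulsivity or aggression may also remove some ADHD presentations, so the upper part of the assumed 30-70% range may be too high. It does not bring the share to zero, since the same list expressly admits ADHD and OCD.

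**Conclusion.** The point holds for the non-randomised healthy-control contrast only. The article fixes asymmetric eligibility and names at most age and gender for matching and adjustment, so the planned contrast carries the extra term p × d. This is not a mere omission of detail that an analysis plan would supply.

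The size is unknown. Under the assumptions shown, it ranges from negligible (0.09 SD, 7% rejection) to material (0.35 SD, 34% rejection, or 30% with 34 scans per group). The 34% is the worst corner of assumed inputs without multiplicity correction and should not be quoted alone. The point is a cheap improvement to what the imaging comparison can conclude, not a fault in the randomised trial.

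**What to change.** 1. **Study design, baseline data.** Record current ADHD/OCD diagnosis and psychotropic medication as analysable baseline variables for each HFA child.
2. **Statistical analysis.** Pre-specify a companion HFA-versus-control contrast on baseline scans, restricted to HFA children without ADHD/OCD. Preferably pool both arms, since baseline precedes treatment. Report its estimate and confidence interval beside the overall contrast.
3. **Wording of conclusions.** Describe the overall contrast as HFA as enrolled, including ADHD/OCD, versus healthy. Attribute a difference to HFA itself only with support from the restricted estimate.

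Eligibility and the randomised population stay as they are. The cost is two recorded items, one of which the psychiatrists already assess, and one further analysis. The restricted contrast is less precise, and at a high comorbid share considerably so. It should be labelled a sensitivity check read from its confidence interval, not a powered test. A restricted estimate that is merely non-significant does not show that the overall difference was due to comorbidity.

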### Interventions

Inclusion of patients with HFA will be randomized into one of two groups. For the active group, patients will be subjected to a 25 Hz stimulation frequency, 250 s pulse width, and a 30-s on/30-s off cycle for a total of 2 hours divided into four 30-minute periods. Patients remain quiet during each 30-minute session. The stimulation intensity will be adjusted to a level where patients experience the maximum tolerable intensity of pain (43–45). In contrast, the sham group will undergo a placebo procedure designed to mimic the active treatment condition. The sham group will be positioned anatomically identical to the active treatment group, receiving the same duration of treatment. However, the stimulation frequency will be set at 1 Hz, and the intensity level will only elicit the minimum perceptible tingling sensation, creating the illusion of active stimulation. The National Institutes for Food and Drug Control (NIFDC)-certified taVNS device TVNS-100 (Xinzhile, Jiangxi, China) will be utilized for the taVNS procedure, with electrodes placed on both the inner and outer surfaces of the tragus in bilateral ears (43). Patients and caregivers will receive professional instructions on how to operate the stimulator and then perform the stimulation by themselves routinely. In addition, patients and caregivers will be instructed to promptly monitor and report any potential side effects, such as headache, tinnitus, vertigo, or nausea, to their doctors during or after stimulation. Depending on the situation, the stimulation intensity may be adjusted, or the stimulation may be stopped.

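### Poor adherence and undefined biased results count as withdrawal after randomisation, so scores can be lost for reasons linked to arm or outcome

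*Protocol article*

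**What the plan says.** The section on recruitment of participants lists discontinuation and withdrawal criteria for the patients. One item reads: "poor adherence, and biased results will be regarded as withdrawing from the study". Acute illness and self-withdrawal appear as separate items, so this one reaches children who did not choose to leave.

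The timing is set in the Study design section: "Following the baseline period, patients will be assigned to one of the two treatment groups randomly". Clinical scales are then taken at W4, W12, W16 and W24 (Table 1).

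On children who leave, Study design promises that "all dropouts will be documented and reported, specifying the reasons for their withdrawal". On blinding it says: "Only the technicians performing the taVNS procedure and the physician assigning the randomization without patient contact will be aware of the group information". Clinical endpoints are rated by blinded observers. Nothing says who applies the withdrawal rule.

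Under Interventions, intensity in the active arm is raised to the point where "patients experience the maximum tolerable intensity of pain", while in the sham arm "the intensity level will only elicit the minimum perceptible tingling sensation". Families are taught to use the device and "then perform the stimulation by themselves routinely".

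For efficacy on the clinical scales, the Statistical analysis section says that "paired samples t-tests will then be used to examine the differences between mean scores before and after the taVNS intervention".

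**The concern.** Randomisation protects the comparison only while children stay in it for reasons unrelated to arm and outcome. Here a protocol rule ends participation for two reasons that may be related to both.

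Poor adherence could differ by arm, because the two arms receive very different sensations and families deliver the treatment themselves over 12 weeks. It could also be related to the score: the CABS is completed by parents, so a family's motivation may affect both how much stimulation is given and how the child is rated.

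The term biased results carries a different risk. Without a definition, a named decision-maker or a statement of blinding, the wording leaves room for a child to be removed because of the data obtained.

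The rule acts during the trial. If a child is treated as withdrawn at, say, W6, the W12 to W24 assessments are not made, and no later analysis plan can recover them.

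**Working it through.** **1. The plan's own figures.** From Sample size estimation: mean paired difference 5, SD 8, alpha 0.05 (two-sided assumed, as sidedness is not stated), power 0.90.

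- n = ((1.960 + 1.282) × 8/5)² = 26.9, so 27
- 20% dropout: 27 / 0.80 = 33.75, so 34
- 15% invalid MRI: 34 / 0.85 = 40

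The plan's 34 and 40 per group are reproduced. Of 40 children, the 20% dropout allowance is 8 per arm. That allowance covers lost precision. It does nothing about which children are lost.

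**2. What the rule does to the stated test.** A paired before/after t-test at W12 needs a baseline and a W12 score. A child withdrawn before W12 lacks the second and cannot enter it. A child withdrawn after W12 has the score, and the article does not say whether it is used.

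**3. Size of the adherence part, under assumptions.** Assume no true effect, change scores with SD 8 (positive meaning improvement), and a correlation r between adherence and improvement. Excluding the lowest fraction f of adherers shifts an arm's mean by

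8 × r × h(f), where h(f) = φ(z_f) / (1 − f).

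- h(0.10) = 0.1755 / 0.90 = 0.195
- h(0.25) = 0.3178 / 0.75 = 0.424
- h(0.30) = 0.3477 / 0.70 = 0.497

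The false active-versus-sham difference is 8 × r × (h(active) − h(sham)). The simulation columns use 40 per arm, 40,000 runs and a two-sample t-test between arms.

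| Excluded active / sham | r | Formula | Simulated bias | Simulated type I error |
|---|---|---|---|---|
| 25% / 10% | 0.3 | 0.55 | 0.53 | 0.06 |
| 30% / 10% | 0.3 | 0.72 | 0.70 | 0.07 |
| 25% / 10% | 0.5 | 0.91 | 0.90 | 0.08 |
| 30% / 10% | 0.5 | 1.21 | 1.18 | 0.10 |
| 20% / 20% | 0.3-0.5 | 0 | about 0 | 0.05-0.06 |

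The range is therefore about 0.5 to 1.2 CABS points against a planning difference of 5, that is, 10% to 24% of it. The exclusion rates and correlations are assumptions, as the article gives no adherence figures by arm.

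**4. The part on biased results.** No size is calculated, because the article does not say what the term means or how often it would apply.

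**The case against.** Several points on the other side stand.

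- **Withdrawal is not deletion.** A reader might infer that affected children vanish from the analysis altogether. The article does not say that collected data are removed, and an analysis plan not shown here may keep them.
- **The term may be innocent.** A reader might infer that scores are to be discarded for their value. The list item is loosely worded and may mean invalid assessments, or poor adherence that makes results unreliable. It mentions neither the size nor the direction of a score.
- **Unequal adherence is not shown.** Families are blinded, and intensity may be adjusted for side effects. Sham families might also lose interest. A daily burden of two hours is an inference too: the article gives a two-hour total in four sessions without stating per day.
- **The calculation concerns a between-arm contrast.** For the clinical scores the article states only paired before/after tests, so the type I errors above do not describe the test as written.
- **Analysis sets may be defined elsewhere.** A condensed article commonly leaves them to the full protocol or analysis plan, so the absence of a named analysis set is not itself a fault.
- **Partial safeguards exist.** Observers are blinded and reasons for dropout are reported.

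What remains is the rule itself. It is stated, it applies after randomisation, it covers children who have not asked to leave, and one of its two criteria is undefined. Blinded rating and reporting of reasons do not restore an assessment that was never made.

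**Conclusion.** The point holds in a limited form. The article fixes a withdrawal rule under which poor adherence and undefined biased results end a child's participation after randomisation. Children removed before W12 cannot contribute to the W12 before/after test, and the wording allows, without establishing, removal on the basis of results.

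The adherence part is modest: about 0.5 to 1.2 CABS points of false active-versus-sham benefit. It rests wholly on assumed unequal exclusion (25-30% against 10%) and an assumed correlation of 0.3-0.5, and it is near zero if exclusion is balanced. The document does not support the stronger claims that data are deleted, that results will be selected by value, or that adherence will in fact be worse in the active arm.

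The point still deserves correction before follow-up is lost, because lost assessments cannot be recovered at the analysis stage.

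**What to change.** - Delete biased results as a withdrawal criterion, or replace it with objective data-quality rules, written in advance and applied blind to arm by a named role.
- State that poor adherence is recorded but does not end follow-up, and that assessments continue to W24 unless consent is withdrawn.
- State that data collected before any withdrawal are kept.
- Make the primary analysis all randomised children in their randomised arm. Use a per-protocol set, with its adherence threshold fixed before unblinding, as a sensitivity analysis only. If the analysis plan already says this, the protocol rule should be brought into line with it.

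The cost is protocol wording and follow-up of non-adherent children at visits already in Table 1. The treatment estimate may be slightly diluted by including them. Decisions to stop stimulation for a child's welfare are not affected.
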